## Abstract

**Introduction:**

The Vagus Nerve Stimulation Therapy System (VNS Therapy) is an adjunctive neuromodulatory therapy that can be efficacious in reducing the frequency and severity of seizures in people with drug-resistant epilepsy (DRE). CORE-VNS aims to examine the long-term safety and clinical outcomes of VNS in people with DRE.

**Methods and analysis:**

The CORE-VNS study is an international, multicentre, prospective, observational, all-comers, post-market registry. People with DRE receiving VNS Therapy for the first time as well as people being reimplanted with VNS Therapy are eligible. Participants have a baseline visit (prior to device implant). They will be followed for a minimum of 36 months and a maximum of 60 months after implant. Analysis endpoints include seizure frequency (average number of events per month), seizure severity (individual-rated categorical outcome including very mild, mild, moderate, severe or very severe) as well as non-seizure outcomes such as adverse events, use of antiseizure medications, use of other non-pharmacological therapies, quality of life, validated measures of quality of sleep (Pittsburgh Sleep Quality Index or Children’s Sleep Habit Questionnaire) and healthcare resource utilisation. While the CORE-VNS registry was not expressly designed to test hypotheses, subgroup analyses and exploratory analysis that require hypothesis testing will be conducted across propensity score matched treatment groups, where possible based on sampling.

**Ethics and dissemination:**

The CORE-VNS registry has already enrolled 823 participants from 61 centres across 15 countries. Once complete, CORE-VNS will represent one of the largest real-world clinical data sets to allow a more comprehensive understanding of the management of DRE with adjunctive VNS. Manuscripts derived from this database will shed important new light on the characteristics of people receiving VNS Therapy; the practical use of VNS across different countries, and factors influencing long-term response.

**Trail registration number:**

NCT03529045.

SummaryCORE-VNS is a global, prospective registry designed to examine the safety and effectiveness of Vagus Nerve Stimulation Therapy System (VNS Therapy) in a real-world setting.This registry captures a wide array of clinical outcome measures to assess the broad scope and impact of VNS Therapy.Herein, prospective analyses are proposed and registered for study using CORE-VNS data, including details regarding planned subpopulation analyses.

## Introduction

Epilepsy is one of the most common serious neurological conditions worldwide, affecting approximately 50 million people and associated with multiple comorbidities and marked psychosocial impact.^1^ About 35% of people living with epilepsy continue to experience seizures despite taking antiseizure medications (ASMs).^2^ Failure to control seizures has serious repercussions that include a higher risk of depression and suicidal mortality, sudden cardiac death, sudden unexpected death in epilepsy, status epilepticus and deaths due to accidents or injuries.^3–6^ Failure to respond to adequate doses of two ASMs constitutes drug-resistant epilepsy (DRE) that merits consideration of non-pharmacological therapies such as surgical resection, dietary therapy and neuromodulatory interventions.^7^

Of the neuromodulatory therapies for epilepsy, the Vagus Nerve Stimulation (VNS) Therapy System is the most widely available. VNS Therapy was approved for use in people with focal and generalised onset seizures in people of all ages in Europe in 1994; for focal-onset seizures in people over the age of 12 the USA in 1997, and is now used across the globe. Since approval, the technology behind the VNS Therapy system has evolved, and indications for use in, for example, the USA have expanded to include applications in children as young as 4 years.

Early advances in VNS Therapy focused largely on improvements in battery life, device size and usability. In recent models, such as AspireSR (Model 106) and SenTiva (Model 1000), additional functionality is available to assist healthcare professionals and improve clinical outcomes. The AutoStim feature was introduced in the AspireSR device to detect and respond to ictal tachycardia, as an indirect biomarker of seizures, and thereby deliver additional stimulation acutely at the time of a seizure to contain seizure propagation in the brain and/or terminate seizures.^8–11^ The AutoStim feature has since been widely adopted, and VNS Therapy that uses the AutoStim feature (AspireSR and SenTiva) is collectively described as responsive VNS. Additionally, the SenTiva system introduced automatic titration using a predefined protocol (scheduled programming) without the need for clinical visits; the ability to deliver separate output parameters for different time periods in a given day (day/night programming); and access to events and trends data to help in patient monitoring (event monitoring) (table 1).

**Table 1 T1:** VNS systems and features

VNS system	AutoStim responsive VNS Therapy	Scheduled Programming	Day/Night Programming	Event Monitoring
Demi-Pulse	–	–	–	–
AspireSR	+	–	–	–
SenTiva	+	+	+	+

VNS, vagus nerve stimulation.

Of these new features, responsive VNS has been the most extensively studied, both in manufacturer-sponsored approval trials as well as in a series of independent prospective and retrospective single-centre cohort studies.^8–19^ These initial investigations suggest that responsive VNS Therapy offers incremental benefit over traditional, non-responsive VNS and may be associated with an earlier onset of effect.

The purpose of CORE-VNS is to assess the broader real-world use of various features of VNS Therapy and their impact. Here we describe the design of the registry and explore some of the hypotheses that we may be able to test.

## Methods and analysis

The CORE-VNS Post-Market Registry aims to collect data on the ‘real life’ global experience of clinical outcomes and safety for people with DRE treated with adjunctive VNS. This registry represents an opportunity to collect a broad set of endpoints, both clinical and health economic, on a large and diverse patient population enabling substantial subpopulation analysis. This global perspective should provide evidence to guide physicians and their patients, regulators and payers/commissioners on the use of VNS for the management of DRE in multiple global regions.

### Participant eligibility and enrolment

Participants considered eligible for enrolment in CORE-VNS must meet the following criteria:

Clinical diagnosis of DRE to be treated with VNS Therapy. People receiving either initial implants or replacement implants are eligible for enrolment.Able and willing to comply with the frequency of protocol-specified visits.Able to voluntarily provide informed consent, by participant or their legal guardian in accordance with institutional policies. In some cases, individuals who are less than 18 years of age may be required to sign an assent affirming their agreement to participate.

There are no specific exclusion criteria for this all-comers registry. Further, local regulatory approvals may limit access to specific VNS Therapy devices for some patient populations.

Participants are considered enrolled on completion of the baseline visit (which includes affirmation of informed consent) and successful implantation of the VNS Therapy system.

There will be no deviation from standard clinical care and only those people who the clinical team decides are suitable for VNS implantation/replacement will be offered the choice to participate. There will be no change to clinical care based on whether an individual chooses to participate or not. Participants may elect to exit the registry at any time without the need to give a reason and with no adverse impact on their clinical care. Participants who are discontinued by the investigators will have reasons documented for discontinuation (eg, early termination or lost to follow-up). Data from participants who withdraw or are withdrawn from the registry will be included to the point of withdrawal.

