### Clinical endpoints

Beyond information on demographics, medical history and genetics (where applicable) in the global DRE population, the registry aims to gather a broad range of clinical outcome measures to assess the purported benefits of VNS. The clinical endpoints of the registry include data collection at baseline as well as 3, 6, 12, 24 and 36 months after implant. Long-term follow-up data may continue annually through 60 months after implant where applicable (table 2).

**Table 2 T2:** Protocol-specified visit schedule and assessments for participants in the CORE-VNS registry. After the first year, patients will return to the clinical site for annual visits, where all endpoint measures will be assessed. At unscheduled visits, only VNS parameter settings, concomitant treatment for epilepsy and safety data will be collected

Target follow-up	Baseline	Implant	Follow-up (post implant)					
	−45 to 5 days before implant	0	Titration visit(s)	3 months (±45 days)	6 months (±45 days)	12/24/36 months (±45 days)	Long-term follow-up *Every 12 months until 60 months or study end (±60 days*)*	Unscheduled visits
Informed consent/assent/data privacy	X							
Inclusion/exclusion criteria	X							
Demographics and medical history	X							
VNS Therapy implant/revision/explant		X	*As needed*	*As needed*	*As needed*	*As needed*	*As needed*	*As needed*
VNS Therapy parameter settings		X	X	X	X	X	X	X
Concomitant treatments for epilepsy†	X			X	X	X	X	
Rescue medication use	X			X	X	X	X	
Seizure frequency	X			X	X	X	X	
Maximum seizure-free period	X			X	X	X	X	
Seizure severity/postictal severity	X			X	X	X	X	
Quality of life	X			X	X	X	X	
Quality of sleep (PSQI or CSHQ)‡	X			X	X	X	X	
Healthcare utilisation	X			X	X	X	X	
VNS Therapy feature use (if applicable)			X	X	X	X	X	X
Deaths and AEs related to VNS (if applicable)§		X	X	X	X	X	X	X
Pregnancy reporting form (if applicable)	*As needed*	*As needed*	*As needed*	*As needed*	*As needed*	*As needed*	*As needed*	*As needed*
Device deficiencies (if applicable)		X	X	X	X	X	X	X
Study completion or withdrawal			*At study exit*	*At study exit*	*At study exit*	*At study exit*	*At study exit*	*At study exit*

*During the long-term follow-up phase, subjects will have yearly follow-up visits until 60 months post implant or until study end (whichever comes first).

†Pharmacological and non-pharmacological.

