Principal analysis of the full cohort data will occur at 3 years of follow-up and will be summarised using descriptive statistics for the relevant analysis population (mSAF or FAS). Intermediate analysis will also be conducted for the full cohort at each year after implant, and topics of this analysis are further described in the following section. Continuous variables will be summarised using the number of observations, mean, median, SD, minimum and maximum values. Categorical variables will be summarised using the number of observations and percentages. Absolute scores and changes from baseline with 95% CIs will be reported for each clinical endpoint at each follow-up visit. VNS-related adverse events, including serious adverse events and deaths, will be presented by system organ class and preferred term as total counts and percentages. These adverse events will be further described by their relationship to VNS implant and/or stimulation and the current status (eg, ongoing, resolved, death, chronic or unknown).

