### The global safety profile of VNS

VNS has been established as a well-tolerated and safe therapy. This finding has been replicated in multicentre randomised controlled trials, registries, single-centre experiences and case series. Most of the global research experience with VNS, however, has occurred in only a few countries. CORE-VNS presents an opportunity to better understand the safety profile of VNS in multiple regions where it has not been previously studied, especially those regions with more recent access to the therapy. Also, certain device components (such as the newest leads) or features (such as responsive VNS) have not been assessed in a comparative fashion versus previous models of these components in a real-world setting.

Patients involved in the study can elect to undergo a device explantation, for any reason. The rationale for explantation is recorded in the case report form associated with that study event. The explantation surgery case report form includes rationale for the explant, such as: death, adverse event(s), lack of efficacy, VNS Therapy no longer desired, MRI, battery depleted, battery nearing depletion, unknown, other.

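### Adverse events and deaths are given as counts and percentages although time at risk differs by participant; comparisons between models or regions need person-year rates and fixed-time cumulative incidence

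*Protocol article*

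**What the plan says.** **Follow-up.** The abstract says of participants: "They will be followed for a minimum of 36 months and a maximum of 60 months after implant". The footnote to Table 2 ends long-term follow-up at month 60 or at study end, whichever is earlier. Under Participant eligibility and enrolment, "Participants may elect to exit the registry at any time without the need to give a reason", and "Data from participants who withdraw or are withdrawn from the registry will be included to the point of withdrawal".

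**Safety.** The section Safety endpoints has adverse events recorded from implant to registry exit, and all deaths captured whatever their cause. Under Statistical analysis, safety is assessed in the modified safety population (mSAF), which is everyone who had an implant procedure, successful or not. VNS-related events, including serious events and deaths, "will be presented by system organ class and preferred term as total counts and percentages". No exposure-adjusted or time-to-event measure is named for them, and no data cut for events.

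**Effectiveness.** "Principal analysis of the full cohort data will occur at 3 years of follow-up", as descriptive statistics. In addition, "Absolute scores and changes from baseline with 95% CIs will be reported for each clinical endpoint at each follow-up visit". The full analysis set (FAS) requires only one post-baseline assessment.

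**Comparisons.** Regional practice and feature use states an interest in regional differences in safety outcomes. The global safety profile of VNS notes that newer components and features have not been compared with earlier ones in real-world use. Device model is a predefined subgroup.

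**The concern.** A percentage with an event has a plain meaning only when everyone has been at risk for about the same time. Here unequal time is built in. Some participants leave before month 36, some stop between months 36 and 60 because the study ends, and some reach month 60. The registry began in 2018 and enrolment closed by the start of June 2021, so entry is staggered by up to about three years.

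Within the whole cohort the result is a figure that is neither the 36-month nor the 60-month risk. Between groups it can mislead. If one model or region contributes mostly later entrants, its percentages are lower simply because it was watched for less time. The article says newer models only recently reached some regions, so a link between model, region and length of follow-up is plausible, though not stated. Deaths are the most exposed, because they can accrue over the whole of follow-up.

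The per-visit changes from baseline raise a related but weaker point. An unmodelled summary at month 36 describes the participants who have a month-36 value, and there is no control group to absorb selective loss.

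**Working it through.** The article gives no event rate, dropout rate or response rate, so there is no figure of its own to reproduce. Apart from the 36- and 60-month limits and N = 823, all inputs below are assumptions.

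**1. Same hazard, different follow-up.** If a share q has had the event by month 36 under a constant hazard, then h = −ln(1 − q)/36 per month, and the share by month 60 is 1 − exp(−60h).

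- q = 5%: 8.2% by month 60
- q = 10%: h = 0.10536/36 = 0.002927; 1 − exp(−0.1756) = 16.1%
- q = 20%: 31.1%

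This is the extreme contrast, with one whole group at 36 months and the other at 60.

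**2. A more realistic mix.** Assume 5 first events per 100 person-years. The share with an event is 1 − exp(−0.05t), with t in years: 7.23% at 18 months, 13.93% at 36 and 22.12% at 60. Let 20% leave at 18 months.

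- All others cut at month 36: 0.8 × 13.93 + 0.2 × 7.23 = 12.6%, against a true 36-month risk of 13.9%.
- Half of the others followed to month 60: 0.8 × (0.5 × 13.93 + 0.5 × 22.12) + 0.2 × 7.23 = 15.9%, which estimates neither 13.9% nor 22.1%.

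Two groups with these two follow-up patterns would differ by 3.3 points (15.9 − 12.6) at the same event rate. At 2 per 100 person-years the pair is 5.2% and 6.7% (1.5 points); at 10 per 100 it is 23.5% and 28.9% (5.4 points). In each pair the rate per person-year is the same in both groups by construction.

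**3. Events clustered around surgery.** Assume 20% have a perioperative event and 1 per 100 person-years have a first event afterwards: 1 − 0.8 × exp(−0.03) = 22.4% at month 36 and 1 − 0.8 × exp(−0.05) = 23.9% at month 60. The gap is 1.5 points.

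**4. Per-visit effectiveness summaries.** Take a responder share purely for illustration; the article defines no responder endpoint for the principal analysis. With dropout d, the whole-cohort share is (1 − d) × stayers' share + d × leavers' share. With 20% dropout (658 of 823 observed) and 60% among stayers:

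- leavers at 60%, 40%, 20% or 0%: whole cohort 60%, 56%, 52% or 48%
- leavers at 100%: 0.8 × 60 + 20 = 68%

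The observed 60% could therefore be 12 points too high, exact, or 8 points too low. Nothing in the document narrows this.

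**The case against.** The strongest reply on safety is that planned follow-up is at least 36 months for everyone and the principal analysis is at 3 years. If events are cut at month 36, only early exits matter, and step 2 shows a modest effect (12.6% against 13.9%). Clustering around surgery shrinks it further. Counts and percentages are also the usual descriptive display, and no sentence says that crude percentages will be the measure for comparing models or regions. Where hypothesis testing is needed, propensity-matched groups are planned. All of this stands and limits the size. However, the article states no cut for events, records them until exit, and names no other measure. Matching on baseline characteristics does not in itself equalise time at risk, and deaths need not cluster around surgery.

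On effectiveness, a reader might infer that the withdrawal rule turns the 36-month result into a completers-only figure that is biased upward, with a rising response over time produced by non-responders leaving. The document does not support that. The withdrawal sentence is ordinary practice: it keeps what was collected and removes nobody. The listed explant reasons include "lack of efficacy, VNS Therapy no longer desired", but also MRI and battery depletion, and they are reasons for removing the device. Table 2 lists explant and study withdrawal as separate rows, and nowhere is explant said to end follow-up. No dropout or outcome rate is given. Missing-data handling may also be in the statistical analysis plan, which the article mentions and which is not shown, so its absence here is not a fault. Numbers of observations and a disposition summary are already planned.

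**Conclusion.** The safety point holds. The stated measure does not account for time at risk in a registry where that time differs by design and by early exit, and any comparison of these percentages between models or regions would mix risk with follow-up.

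Its size rests on assumptions. At identical risk, 10% can become 16.1% in the extreme constant-hazard case, and the mixed-follow-up scenarios give differences of 1.5 to 5.4 points. The effect is small with a common 36-month cut or with perioperative clustering. The purely descriptive totals are not wrong; they are insufficient for comparison.

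On effectiveness, only a supporting remark survives: the per-visit changes describe those still observed at each visit. Neither the direction nor the size of any attrition bias can be derived from the document, so a claim of upward bias should not be made.

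**What to change.** 1. Keep the counts and percentages, and state the follow-up window to which each table refers.
2. Add exposure-adjusted incidence per 100 person-years, and cumulative incidence at fixed times (for example 12, 24, 36 and 60 months) with death as a competing event. Report deaths per person-year and as cumulative mortality at the same times.
3. Use the measures in item 2, not crude percentages, for any comparison between models or regions.
4. As a supporting analysis, accompany the per-visit changes from baseline with a longitudinal mixed model using all FAS visits, on a scale suited to each endpoint. It relies on missingness being explained by the observed data. Coding withdrawals as non-response by reason is of limited use, because participants may leave without giving one.

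The cost is a few sentences of analysis wording and standard programming. Implant and study exit are already recorded in the visit schedule, so no new data collection should be needed beyond event dates, which are assumed to be on the case report forms. Mixed and Cox models are already planned for the titration questions.

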### Clinical sites

The CORE-VNS registry has currently activated 61 clinical sites across 15 countries (figure 1). The sites and investigators supporting this registry are listed in online supplemental appendix A.

10.1136/bmjno-2021-000218.supp1Supplementary data

**Figure 1 F1:**
[figure not shown]
CORE-VNS is a global drug-resistant epilepsy registry that includes sites in Australia, Austria, Belgium, Brazil, Canada, China, India, Israel, Italy, Japan, Netherlands, Poland, Saudi Arabia, UK and the USA. The number listed on or near each highlighted country indicates the number of CORE-VNS sites in that country. A full list of centres and principal investigators can be found in online supplemental appendix A. Note: This map has been adapted from The World Factbook. VNS, vagus nerve stimulation.

### Clinical endpoints

Beyond information on demographics, medical history and genetics (where applicable) in the global DRE population, the registry aims to gather a broad range of clinical outcome measures to assess the purported benefits of VNS. The clinical endpoints of the registry include data collection at baseline as well as 3, 6, 12, 24 and 36 months after implant. Long-term follow-up data may continue annually through 60 months after implant where applicable (table 2).

**Table 2 T2:** Protocol-specified visit schedule and assessments for participants in the CORE-VNS registry. After the first year, patients will return to the clinical site for annual visits, where all endpoint measures will be assessed. At unscheduled visits, only VNS parameter settings, concomitant treatment for epilepsy and safety data will be collected

Target follow-up	Baseline	Implant	Follow-up (post implant)					
	−45 to 5 days before implant	0	Titration visit(s)	3 months (±45 days)	6 months (±45 days)	12/24/36 months (±45 days)	Long-term follow-up *Every 12 months until 60 months or study end (±60 days*)*	Unscheduled visits
Informed consent/assent/data privacy	X							
Inclusion/exclusion criteria	X							
Demographics and medical history	X							
VNS Therapy implant/revision/explant		X	*As needed*	*As needed*	*As needed*	*As needed*	*As needed*	*As needed*
VNS Therapy parameter settings		X	X	X	X	X	X	X
Concomitant treatments for epilepsy†	X			X	X	X	X	
Rescue medication use	X			X	X	X	X	
Seizure frequency	X			X	X	X	X	
Maximum seizure-free period	X			X	X	X	X	
Seizure severity/postictal severity	X			X	X	X	X	
Quality of life	X			X	X	X	X	
Quality of sleep (PSQI or CSHQ)‡	X			X	X	X	X	
Healthcare utilisation	X			X	X	X	X	
VNS Therapy feature use (if applicable)			X	X	X	X	X	X
Deaths and AEs related to VNS (if applicable)§		X	X	X	X	X	X	X
Pregnancy reporting form (if applicable)	*As needed*	*As needed*	*As needed*	*As needed*	*As needed*	*As needed*	*As needed*	*As needed*
Device deficiencies (if applicable)		X	X	X	X	X	X	X
Study completion or withdrawal			*At study exit*	*At study exit*	*At study exit*	*At study exit*	*At study exit*	*At study exit*

*During the long-term follow-up phase, subjects will have yearly follow-up visits until 60 months post implant or until study end (whichever comes first).

†Pharmacological and non-pharmacological.

‡PSQI: Pittsburgh Sleep Quality Index for subjects ≥18 years of age at baseline/CSHQ: Children Sleep Habit Questionnaire for subjects 2–17 years of age at baseline.

§AEs possibly, probably or definitely related to VNS Therapy per investigator assessment (including those with unknown relationship).

AEs, adverse events; CSHQ, Children Sleep Habit Questionnaire; PSQI, Pittsburgh Sleep Quality Index; VNS, vagus nerve stimulation.

Clinical assessments include: average seizure frequency per month for the 3 months prior to each protocol-specified visit and maximum seizure-free period over 90 days prior to each protocol-specified visit. Seizure severity and postictal severity are based on participant-rated categorical outcome (very mild; mild; moderate; severe; and very severe). Quality of life assessment is based on a participant-rated categorical outcome (very good: could hardly be better; pretty good; good and bad parts about equal; pretty bad; or very bad: could hardly be worse). Given the anticipated recruitment and the duration of the study, Likert scales were selected to limit the impact of visit duration on enrolment and participant retention.

On account of previously reported interactions between VNS and sleep apnoea and the limited evidence in this area,^20–22^ quality of sleep assessment was collected through validated scales. Participants who are over 18 years of age at baseline are requested to complete the Pittsburgh Sleep Quality Index (PSQI) at each protocol-specified visit, including baseline.^23^ Participants who are between 2 and 18 years of age at baseline complete the Children’s Sleep Habit Questionnaire.^24–26^ Participants who are less than 2 years of age at baseline are not assessed for sleep quality.

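### The 3-month seizure look-back is not cut at implant, so 3-month visits before about day 90 count pre-implant time as follow-up and dilute the month-3 result

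*Protocol article*

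**What the plan says.** Under Clinical endpoints, seizure frequency is the "average seizure frequency per month for the 3 months prior to each protocol-specified visit", and the companion measure is the "maximum seizure-free period over 90 days prior to each protocol-specified visit". Both rules apply to every scheduled visit alike. The article gives no exception for the first one.

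Table 2 sets the first follow-up visit with seizure assessments at "3 months (±45 days") after implant. The later visits are at "6 months (±45 days") and "12/24/36 months (±45 days"). The baseline visit falls "45 to 5 days before implant".

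Under Statistical analysis, the article commits to reporting each clinical endpoint at every follow-up visit, both as an absolute value and as a change from baseline with a 95% confidence interval. The principal analysis is at 3 years, with intermediate full-cohort analyses at each year. Under Titration guidance and scheduled programming, a Cox model is planned to relate time-to-dose to time-to-response and to contrast titration in under 3 months with titration over more than 6 months.

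**The concern.** The look-back is as long as the nominal time from implant to the first visit, but the visit may come up to 45 days early. When it does, a 90-day period reaches back before implant, and seizures from untreated time are recorded as follow-up.

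The resulting change in seizure frequency is pulled toward no effect, by an amount that depends on the day of the visit. Design limitations states that benefit can only be judged against each participant's own baseline, so no control group shares and offsets the error. The baseline and month-3 periods can even share calendar days.

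At stake are the published month-3 change and any statement about speed of effect. Month 3 is the first scheduled seizure assessment after implant, so a response diluted there may be dated to month 6 in a time-to-response analysis. If early visits are more common in one titration, device or feature group than in another, the dilution will differ between the groups.

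**Working it through.** **Inputs.** Look-back of 3 months, taken as 90 days, and visit windows of ±45 days (Clinical endpoints and Table 2). The article states no figure for the pre-implant share, so there is none to reproduce.

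**Window.** Earliest 3-month visit: 90 − 45 = day 45. Latest: 90 + 45 = day 135.

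**Pre-implant share of the look-back at visit day d:** max(0, 90 − d)/90.

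**Observed reduction.** With a constant seizure rate before implant and a constant true reduction r after it, observed reduction = r × (1 − pre-implant share).

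| Visit day | Pre-implant days | Share | True 50% reads as | True 100% reads as |
|---|---|---|---|---|
| 45 | 45 | 50% | 25% | 50% |
| 60 | 30 | 33% | 33% | 67% |
| 75 | 15 | 17% | 42% | 83% |
| 90 or later | 0 | 0% | 50% | 100% |

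Taking 3 months as 91.3 days barely changes this: the earliest visit has 45/91.3 = 49% pre-implant time.

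**Average over the window.** Actual visit timing is not given. If visits were uniform over days 45 to 135 (assumption), the mean share is (45²/2)/(90 × 90) = 1012.5/8100 = 12.5%. A true 50% reduction then reads as 0.50 × 0.875 = 43.75%, about 44%. Visits clustered at the 90-day target would give less dilution.

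**Effect on a response date.** If response meant a reduction of at least 50% (assumption; the article gives no threshold), the true reduction needed to register would be 0.50/(d/90): 100% at day 45, 75% at day 60 and 60% at day 75.

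**Overlap with baseline.** With a baseline visit at day −5, its look-back runs from day −95 to day −5. A day-45 visit looks back from day −45 to day 45. The two share days −45 to −5, which is 40 days. With a baseline visit at day −45 they share none.

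**Later visits.** Earliest 6-month visit: 180 − 45 = day 135, look-back from day 45. Earliest 12-month visit: 365 − 45 = day 320, look-back from day 230. Earliest 36-month visit: 1095 − 45 = day 1050, look-back from day 960. None contains pre-implant time.

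**Seizure-free period.** The same days enter the 90-day window, but a longest run is not an average, so the proportional formula does not apply to it. A run that began before implant can be counted as follow-up.

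**The case against.** The strongest reply is that the problem is confined to one secondary time point. The principal analysis is at 3 years and the intermediate analyses are yearly, and none of them contains pre-implant time. The day-45 figure is the extreme. Under even spacing the average loss is about 6 percentage points on a true 50%, and less if visits cluster at the target. The pandemic delays described under Design limitations concern titration visits; if they also delayed 3-month visits, the overlap would shrink. All of this stands and limits the size of the point. It does not remove it, because the article commits to reporting month 3 and states a look-back rule that gives the wrong period for early visits. A truncation rule may exist in a document not shown. If so, the article's wording needs to match it.

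A reader might infer that the seizure results as a whole are biased. The date arithmetic does not support that: every visit after month 3 is clear of implant.

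A reader might also infer a bias in severity, because "Seizure severity and postictal severity are based on participant-rated categorical outcome (very mild; mild; moderate; severe; and very severe") offers no level for someone without seizures. The article does not support that either. An option or rule for such participants commonly sits in the case report form or analysis plan. Severity among seizures that occur is a legitimate quantity, and seizure freedom is already captured by frequency and by the seizure-free period. No proportion of seizure-free participants is given from which an effect could be computed.

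**Conclusion.** The point holds for the 3-month seizure frequency and seizure-free period, for visits before about day 90, and for analyses that draw on them, notably time-to-response. For frequency the error runs toward no change. A true 50% reduction reads as 25% at day 45, 33% at day 60 and 42% at day 75, and as about 44% on average if visits are uniform over the window.

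The pre-implant shares are date arithmetic and need no assumption beyond a 90-day look-back. The diluted reductions assume constant rates before and after implant. If the effect builds up after implant, r stands for the average effect over the post-implant days. The overall average depends on visit timing, which the article does not give. Results at month 6 and later, including the 3-year principal analysis, are unaffected.

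**What to change.** For the 3-month visit, limit the seizure-frequency look-back to post-implant days, and divide by days since implant when that is under 90, wherever the recorded data allow it. The article describes a monthly average and no dated seizure counts, so this may not be possible for data already collected.

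Where only a monthly average was stored, report the 3-month frequency and seizure-free-period results for all visits and also restricted to visits on or after day 90. State how many visits the restriction excludes. Do not base claims about onset or time-to-response on the earlier visits.

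Do not simply cap the seizure-free period at days since implant. A day-45 value could then be at most 45, against a possible 90 at baseline, which would build in an apparent worsening. The restricted summary avoids this.

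The cost is a derivation rule and an extra table, needing only implant and visit dates. The downside is fewer participants in the restricted summary. Under uniform timing, (90 − 45)/(135 − 45) = 50% of visits would be excluded, and those kept would be selected by visit timing. That is why it belongs beside the full summary and should not replace it.
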